#### Exclusion criteria

Pregnant or breastfeeding.Underlying primary immunodeficiency.Received or likely to receive IVIg/SCIg.Projected treatment is likely to involve plasma exchange.Contraindication to receipt of a COVID-19 vaccine.

### Intervention and comparator

Only participants with a systemic autoimmune/inflammatory disease or a haemato-oncology condition (Group 1) will receive the DT intervention. Participants randomised to the deferred COVID-19 booster will receive the DT booster prior to starting immunosuppressive therapy and those randomised to the immediate COVID-19 booster will receive the DT booster at 6 months.

Although all participants will receive a COVID-19 booster, it is not a study intervention. It will be administered at vaccination sites in general practice sites and pharmacies and provided free of charge as part of the Australian Government National COVID-19 Vaccine Programme.

### Criteria for discontinuing or modifying allocated intervention

Study participation is voluntary, and participants can withdraw consent or cease participation at any time without penalty. Investigators may also withdraw participants for several reasons including progression of underlying disease; occurrence of unacceptable adverse events (AEs); continued participation is considered not to be in the participant’s best interest; or either party wishes to cease participation.

### Strategies to improve adherence to intervention protocols

Investigators and study coordinators will encourage participant attendance at follow-up visits to ensure data collection is maximised. Following randomisation participants will be provided with a schedule detailing dates of study visits. To reduce the number of on-site visits, the visit schedule permits screening and randomisation to be conducted on the same day. Additionally, participants randomised to the deferred COVID-19 booster can receive their DT booster at this time further reducing the need for a return visit. Study staff will ensure data on AEs, and health questionnaires are completed during study visits and will assist in ensuring questionnaire completion. As study visit attendance can incur expenses, participants will be reimbursed in the form of a $30 gift card for each on-site visit attendance.

### Concomitant care permitted or prohibited during the trial

During the trial participants will receive standard of care management for their study qualifying medical condition as well as other medical conditions that might arise. Participants should not receive additional COVID-19 boosters during the trial as it will alter assessment of the immune responses to the COVID-19 booster administered on-study. All doses of tixagevimab/cilgavimab (Evusheld) administered for COVID-19 prevention will be recorded in case report forms. For patients who receive tixagevimab/cilgavimab, the anti-spike IgG assays will be modified to discriminate between host-derived anti-spike IgG and the synthetic monoclonal antibodies. This can be achieved because tixagevimab/cilgavimab has been modified to not bind to Fc gamma receptors (FcγRs).^21^ The FcγR is an endogenous receptor that binds naturally occurring antibodies produced by the host. The modifications made to tixagevimab/cilgavimab were aimed at reducing antibody-dependent cellular cytotoxicity and related inflammation.^21^ Therefore, including a ‘positive selection’ FcγR binding step in the anti-spike IgG assay allows for the detection of host-produced anti-spike IgG and not the synthetic antibodies.

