### Objectives

This study aims to evaluate the optimal timing of a COVID-19 booster vaccination in adults commencing moderate-to-severe immunosuppression for either an autoimmune/inflammatory disease or a haematological malignancy or who have undergone a bone marrow transplant in the previous 9 months. Efficacy will be assessed primarily by measuring the anti-SARS-CoV-2 neutralising antibody (NAb) response to the booster over 12 months. Other correlates of protective immunity as well as safety and quality of life will be assessed.

Delaying administration of the COVID-19 booster in the deferred arms may lead to higher numbers of breakthrough COVID-19 infections in these arms. The Data Safety Management Board (DSMB) will closely monitor on-study infections and advise the principal investigator and Protocol Steering Committee (PSC) should there be any concerns.

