### Outcomes

The primary outcome will be the integrated time-weighted area under the curve (AUC) anti-SARS-CoV-2 NAb response over 12 months from a SARS-CoV-2 booster as assessed by a high-throughput SARS-CoV-2 NAb platform assay developed by our group.^22^,^24^ The assay involves culturing a cell-line that is hyper-permissible to SARS-CoV-2 through the expression of ACE2 and transmembrane serine protease 2 receptors. Serial dilutions of patient serum are then introduced to the cell culture wells in addition to homogenous concentrations of SARS-CoV-2 virions including variants of concern. Anti-spike IgG present in the patient serum acts to block viral entry into the cell. The assay readout is the infectious dose 50% (ID_50_), the viral concentration required to obtain 50% cellular death.

Secondary outcomes include laboratory, safety and clinical/biological outcomes:

Laboratory outcomes:

NAb response to a tetanus toxoid booster integrated over 12 months.Responses to the COVID-19 vaccine includingBreadth of NAb against SARS-CoV-2 variants of concern.Kinetics of NAb over time including responses to variants of concern.Memory T cell, B cell and natural killer (NK) cell responses to peptide sets representing different domains of the SARS-CoV-2 spike protein.Immunological responses as assessed above in populations stratified by broad study-qualifying disease type and different modes of immunosuppression employed such as chemotherapy, BMT, B-cell depleting therapies and cytokine inhibition.

Safety outcomes:

Local and systemic AEs that occur in the 7 days following the DT and COVID-19 vaccinations.AEs following immunisation and adverse drug reactions following immunisation for the duration of the study.COVID-19 vaccine-induced disease flares.On-study PCR-confirmed or rapid antigen-confirmed SARS-CoV-2 infections.All on-study pregnancies.

Clinical/biological outcomes:

Health quality of life scores (EQ-5D-3L) at weeks 0, 24 and 48.Impact of immunosuppression on vaccine protection over time will be assessed by modelling:Level of protection over time based on NAb levels.Boosting and decay of anti-spike IgG, specific memory B, T and NK cell responses.Inform policies on the timing of additional COVID-19 boosters in vulnerable populations about to commence immunosuppression or following BMT.

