### Sample size

The maximum sample size is 320 participants, 280 in the systemic autoimmunity and haemato-oncology group and 40 in the BMT recipient group. This sample size is based on previously calculated integrated time-weighted AUC of live anti-SARS-CoV-2 NAb titres following two SARS-CoV-2 vaccinations in healthy adults^25^ and patients infected with COVID-19.^26 27^ SD calculated from these datasets were 0.11 log_10_ and 0.12 log_10_, respectively. Assuming an SD of 0.12 log_10_, the study will have over 90% power to detect a 0.13 log_10_ difference in time weighted AUC log_10_ change from baseline (2-alpha=5%) within each sub-stratum of 40 participants. This corresponds to a 35% difference in live virus neutralisation titre between randomised arms. Time-weighted AUC allows for varying of follow-up of participants due to missed visits, loss to follow-up or death. We conservatively estimate overall lost to follow-up to be 10% and mortality 1% balanced across randomised sub-strata.

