### Randomisation

#### Sequence generation

Participants will be assigned to a study group based on their study-qualifying medical condition (table 1) using a central computer-generated randomisation sequence with a blocking factor of four created by the study statistician.

Participants in Group 1 will be stratified into one of two supra-stratum, haematological malignancy or systemic autoimmunity and then to sub-strata based on their planned treatment. Sub-strata include: haematological malignancy—chemotherapy; autoimmunity—B-cell depletion therapies; autoimmunity—anti-metabolite therapies; autoimmunity—TNFα-inhibition; autoimmunity—cyclophosphamide or alemtuzumab; autoimmunity—JAKi; autoimmunity—anti IL-17/23 monoclonal antibodies (table 1).

Group 1 participants will be randomised in a 1:1 ratio to receive either a COVID-19 booster at week 0 and a DT booster at week 24 (Arm A: immediate booster), or a DT booster at week 0 and a COVID-19 booster at week 24 (Arm B: deferred booster) (figure 1). Randomisation will be conducted using a central computer-generated random allocation algorithm using blocks and stratified by sub-strata population.

Group 2 has no sub-strata and participants will be randomised in a 1:1 ratio to receive either an immediate COVID-19 booster at week 0 (Arm C), or a deferred COVID-19 booster at week 24 (Arm D) (figure 1).

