### Statistical methods

#### Statistical methods for analysing primary and secondary outcomes

Baseline participant characteristics will be summarised by randomised arm for each sub-stratum separately and combined. Primary analyses will compare immunogenicity endpoints between randomised arms on an intention-to-treat basis, that is comparing participants as randomised regardless of whether they received immediate or deferred vaccinations according to the protocol. Log_10_ NAb titres will be summarised at each time point and presented graphically within each stratum. The primary outcome will be time-weighted AUC change from baseline in anti-SARS-CoV-2 log_10_ NAb titre over 12 months. The primary analysis will follow a modified intention to treat approach (mITT) and include all randomised participants with a baseline visit and at least one post baseline time point measured. This approach allows for the inclusion of all participants, even with partial follow-up. The AUC will be calculated for each participant using the trapezoidal rule based on all available data. To assess for bias due to missing data, a secondary analysis which will only include patients who completed the study and have no missing data will be performed. These results will be compared with the mITT analysis. Additionally, if the proportion of patients with missing data is over-represented in one study arm, additional sensitivity analyses will be performed. Randomised arms will be compared within each treatment stratum separately using simple, unadjusted two-sample t-tests. In the event of unbalanced baseline characteristics, adjusted comparisons using linear regression methods may be performed. Results will be presented as mean differences, 95% CIs and p values. There will be no adjustment of p values and CIs for multiple comparisons across the seven sub-strata. In addition to analyses within strata, analyses combining all strata will be performed. Analyses will test for different effects of immediate versus deferred vaccination in separate strata by testing for interactions between strata and randomised arm. These results will be presented as forest plots, by strata and overall. Analysis for Group 2 participants will be presented independently using similar approaches as above as appropriate.

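### The only stated correction for tixagevimab/cilgavimab is in the anti-spike IgG assay, so as written the monoclonal's activity, like infection-driven titre, counts in the primary neutralisation AUC

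*Protocol article*

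**What the plan says.** Under Concomitant care, the Protocol article bars further COVID-19 boosters because they would change the response being measured. It does not bar tixagevimab/cilgavimab; doses are recorded. The one protection described is this: "For patients who receive tixagevimab/cilgavimab, the anti-spike IgG assays will be modified to discriminate between host-derived anti-spike IgG and the synthetic monoclonal antibodies". The means is an Fcγ-receptor (FcγR) positive-selection step, which the section places in the anti-spike IgG assay.

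Under Outcomes, the primary endpoint is a neutralisation platform: dilutions of patient serum are added to cultured cells with virus, and cell death is read. The mechanism is given as follows: "Anti-spike IgG present in the patient serum acts to block viral entry into the cell". No selection or depletion step is described for this assay.

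On infection, Objectives says: "Delaying administration of the COVID-19 booster in the deferred arms may lead to higher numbers of breakthrough COVID-19 infections in these arms". Infections are then listed as a safety outcome and reviewed by the DSMB.

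Under Statistical methods: "The AUC will be calculated for each participant using the trapezoidal rule based on all available data". The primary set is a modified intention-to-treat set. The supporting analyses named there and in the section on non-adherence and missing data cover completers, missing-data imbalance, baseline adjustment and per-protocol adherence. None names infection or receipt of the monoclonal.

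**The concern.** A neutralisation assay registers any antibody in the serum that blocks the virus. On the protocol's own account, the monoclonal was altered so that it does not bind FcγR. That makes it separable in an assay with an FcγR step, but does not remove its neutralising activity from serum tested without one. The sponsor recognised the problem, and the stated remedy does not reach the endpoint that decides the trial.

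Infection is a second source of titre that the booster did not cause. The reason given for barring extra boosters applies equally to it, yet no analysis separates it out.

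Two things are at stake. Extra titre in some participants widens the spread of the AUC, whichever arm they are in. If such participants are more common in one arm, the mean contrast moves as well. The design difference is only 0.13 log10, so neither effect need be large to matter.

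**Working it through.** **Inputs from the Protocol article (Sample size; Sequence generation).** "Assuming an SD of 0.12 log_10"; "over 90% power to detect a 0.13 log_10_ difference in time weighted AUC log_10_ change from baseline (2-alpha=5%) within each sub-stratum of 40 participants"; 1:1 allocation, hence 20 v 20 in a sub-stratum and 140 v 140 in Group 1 as a whole.

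**The plan's own figure.** Power for 0.13 at SD 0.12 with 20 per arm and two-sided 5% is 92.9% by the normal approximation and 91.6% by the noncentral t. Both agree with the stated figure of over 90%. 10^0.13 = 1.349, which matches the stated 35%. The sample size calculation is not in error on its own inputs.

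**Assumed inputs.** The documents give no infection rate, no frequency of monoclonal use and no titre gain. Let p be the excess share of one arm with non-booster antibody, g the log10 gain and f the share of follow-up affected.

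**Shift in the contrast = p × g × f**, with g = 1.0 and f = 0.5:

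| p | Shift (log10) | Share of 0.13 |
|---|---|---|
| 5% | 0.05 × 1.0 × 0.5 = 0.025 | 19% |
| 10% | 0.10 × 1.0 × 0.5 = 0.05 | 38% |
| 20% | 0.20 × 1.0 × 0.5 = 0.10 | 77% |

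Over p = 5–20%, g = 0.5–1.5 and f = 25–50%, the shift runs from 0.006 to 0.15 log10, or 5% to 115% of 0.13.

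**Middle case (p = 10%), shift opposing a true difference of 0.13.** The remaining difference is 0.13 − 0.05 = 0.08. Sub-stratum power is 53.8% with the SD held at 0.12. Adding the mixture variance, the affected arm has variance 0.12² + 0.10 × 0.90 × 0.5² = 0.0369; the average with 0.0144 is 0.02565, the SD is 0.160 and power is 33.7%.

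**Middle case with no true timing effect, SD 0.12.** A shift of 0.05 makes the two-sided 5% test reject about 25% of the time at 20 v 20 and about 93% at 140 v 140.

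**Equal frequency q in both arms.** There is no mean shift, only spread: SD = √(0.12² + q(1−q)e²), where e is the gain in the AUC.

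- q = 5%, e = 0.25: SD 0.132, power 86.0%.
- q = 10%, e = 0.5: SD 0.192, power 55.0%.
- q = 25%, e = 0.25 to 0.5: SD 0.162 to 0.248.

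The power figures treat the mixture as normal, so they are approximate.

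**Direction for infection.** Outcomes counts the 12 months from a COVID-19 booster; Statistical methods uses change from baseline. If the origin is week 0, excess infections in the deferred arm raise its AUC and dilute an advantage of the immediate booster. If the origin is the booster date, infections before week 24 raise the deferred arm's baseline and lower its change, so the bias runs the other way.

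**The case against.** The article uses the term anti-spike IgG loosely. Outcomes explains neutralisation itself by that term, and the Abstract frames the whole question in it. The authors may therefore have meant the FcγR step to cover the neutralisation platform, whose details lie in cited papers that are not shown. That intent is possible, but it does not put the step in the primary assay. The text locates it in the IgG assay and should say otherwise if that is what is done.

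On infection the objection is stronger. Keeping post-infection titres in an as-randomised comparison is defensible, because infections that follow from deferral are part of the timing strategy. Dropping them conditions on an event after randomisation. A fuller statistical analysis plan is promised and may add a sensitivity analysis. This stands, and is why the all-data AUC should remain primary with respect to infection.

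A reader might also infer that the deferred arms will have more infections and more monoclonal use, so that the contrast must shrink or reverse. The documents do not support that. Objectives says only that infections may be more frequent. Nothing suggests that monoclonal use will differ by arm; open allocation merely permits it. The deferred arms are themselves boosted at week 24, and the sign of any infection bias depends on the time origin.

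**Conclusion.** The point on the monoclonal holds on the text: the one correction described is attached to an assay other than the primary, and the primary AUC takes all available titres. Its effect is added variance, and bias only if use differs by arm. The infection point is weaker. Those titres also enter the AUC, possibly unequally by arm, but retaining them is a legitimate choice that needs a supplementary analysis beside it.

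The size cannot be derived from the documents. The 0.05 log10 shift (38% of 0.13; 0.025 to 0.10 for a 5- to 20-point excess) follows from an assumed 1.0 log10 gain over half of follow-up, and the wider range shows how far the answer depends on such inputs. It would be wrong to conclude that the stated power is miscalculated, since it reproduces, or that the trapezoidal AUC and t-test must give way to a repeated-measures model, since neither point requires it.

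**What to change.** 1. **Monoclonal.** In Concomitant care and Outcomes, state that the FcγR selection step is applied to serum before the neutralisation assay, if that is done and validated. Otherwise, exclude neutralisation titres after any tixagevimab/cilgavimab dose from the primary AUC and report the all-data AUC beside it.
2. **Infection.** Keep the as-randomised all-data AUC as primary. Pre-specify a supplementary analysis that drops titres after the first PCR- or rapid-antigen-confirmed infection or off-schedule COVID-19 booster. Report event counts by arm and by 24-week period.

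The trapezoidal AUC and the t-test stay. The cost is wording before data lock: monoclonal doses, infections and COVID-19 vaccinations are already collected. The downside is that some titres are discarded, and a participant left with no post-baseline titre would drop out of that analysis. The supplementary result conditions on a post-randomisation event and assumes missing-at-random, so it should be read beside the all-data result, not in place of it.

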### Outcomes

The primary outcome will be the integrated time-weighted area under the curve (AUC) anti-SARS-CoV-2 NAb response over 12 months from a SARS-CoV-2 booster as assessed by a high-throughput SARS-CoV-2 NAb platform assay developed by our group.^22^,^24^ The assay involves culturing a cell-line that is hyper-permissible to SARS-CoV-2 through the expression of ACE2 and transmembrane serine protease 2 receptors. Serial dilutions of patient serum are then introduced to the cell culture wells in addition to homogenous concentrations of SARS-CoV-2 virions including variants of concern. Anti-spike IgG present in the patient serum acts to block viral entry into the cell. The assay readout is the infectious dose 50% (ID_50_), the viral concentration required to obtain 50% cellular death.

Secondary outcomes include laboratory, safety and clinical/biological outcomes:

Laboratory outcomes:

NAb response to a tetanus toxoid booster integrated over 12 months.Responses to the COVID-19 vaccine includingBreadth of NAb against SARS-CoV-2 variants of concern.Kinetics of NAb over time including responses to variants of concern.Memory T cell, B cell and natural killer (NK) cell responses to peptide sets representing different domains of the SARS-CoV-2 spike protein.Immunological responses as assessed above in populations stratified by broad study-qualifying disease type and different modes of immunosuppression employed such as chemotherapy, BMT, B-cell depleting therapies and cytokine inhibition.

Safety outcomes:

Local and systemic AEs that occur in the 7 days following the DT and COVID-19 vaccinations.AEs following immunisation and adverse drug reactions following immunisation for the duration of the study.COVID-19 vaccine-induced disease flares.On-study PCR-confirmed or rapid antigen-confirmed SARS-CoV-2 infections.All on-study pregnancies.

Clinical/biological outcomes:

Health quality of life scores (EQ-5D-3L) at weeks 0, 24 and 48.Impact of immunosuppression on vaccine protection over time will be assessed by modelling:Level of protection over time based on NAb levels.Boosting and decay of anti-spike IgG, specific memory B, T and NK cell responses.Inform policies on the timing of additional COVID-19 boosters in vulnerable populations about to commence immunosuppression or following BMT.

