## Abstract

**Introduction:**

Immunosuppression is associated with an increased risk of delayed SARS-CoV-2 viral clearance, severe COVID-19 and related death. This heterogeneous group of affected patients includes but is not limited to those with a haematological malignancy, people on immunosuppressive therapy for the treatment of autoimmune/inflammatory diseases and those following bone marrow transplantation (BMT). Immunosuppression is associated with decreased rates of anti-spike IgG seroconversion following COVID-19 vaccination. While clinical guidelines have been established to guide vaccination pre-splenectomy and post-BMT, there are limited data to guide timing of COVID-19 or other booster vaccines in adults commencing new or intensified moderate to severe immunosuppression. The comparison of immunity-boosting regimens for COVID-19 upon initiation of immunosuppressive therapy (CIRCUIT) study was designed to address this knowledge gap. CIRCUIT investigates whether administration of a third (or subsequent) COVID-19 booster vaccine ≤2 weeks prior to immunosuppression provides greater anti-spike IgG-mediated immunity than a booster given 24 weeks after new or intensified immunosuppression, that is, week 24 timepoint (Group 1; n=280). Additionally, the research will investigate whether giving a fourth post-BMT COVID-19 booster vaccine at 9 months post-transplant provides greater anti-spike IgG-mediated immunity than a booster given 15 months post-transplant (Group 2; n=40).

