### Explanation for choice of comparator

Group 1 participants will be randomised to receive either a baseline (week 0) COVID-19 booster prior to commencing new or intensified immunosuppressive therapy and a DT booster at week 24 (Arm A) or a baseline DT booster and a week 24 COVID-19 booster (Arm B).

Participants in Group 2 will have undergone a BMT in the previous 9 months and received three post-BMT COVID-19 vaccines. These participants will be randomised to either receive their fourth post-BMT COVID-19 vaccine at baseline (week 0) (Arm C) or at week 24 (Arm D).

Due to the evolving nature of COVID-19 vaccine development, the study will accept any COVID-19 vaccine licensed for use in Australia. Due to established guidelines on post-BMT vaccination including diphtheria and tetanus, only COVID-19 boosters will be studied in Group 2.^16^

The DT vaccine was selected as the comparator for the COVID-19 vaccine. The DT vaccine is protein-based and stimulates an immune response via a different mechanism to that of currently available mRNA-based COVID-19 vaccines. The study will assess whether the findings that relate to the optimal timing of the COVID-19 booster also apply to more traditional protein-based vaccines. If this is found to be the case, then the study results may have broader implications for vaccinology and optimal clinical guidelines.

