### Participant timeline

The study design and participant timeline are shown in figure 1. Participants in Group 1 will have up to 11 visits over 12 months and those in Group 2 a maximum of 10.

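### The primary antibody AUC is given two time origins, booster and week 0, which differ by 24 weeks in the deferred arms and can point to opposite winners

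*Protocol article*

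**What the plan says.** The Outcomes section of the protocol article, like the methods paragraph of the Abstract, counts time from vaccination: "The primary outcome will be the integrated time-weighted area under the curve (AUC) anti-SARS-CoV-2 NAb response over 12 months from a SARS-CoV-2 booster". The Objectives section likewise speaks of the response to the booster over 12 months.

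The section on statistical methods for primary and secondary outcomes counts from baseline: "The primary outcome will be time-weighted AUC change from baseline in anti-SARS-CoV-2 log_10_ NAb titre over 12 months". The Sample size section also powers a change from baseline. The section explaining the comparator equates baseline with week 0.

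Under Sequence generation, Arm B receives "a DT booster at week 0 and a COVID-19 booster at week 24". Arm D also has its COVID-19 booster at week 24, while Arms A and C have it at week 0.

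On follow-up, the Participant timeline says: "Participants in Group 1 will have up to 11 visits over 12 months". The last assessment with a stated week is quality of life at week 48 (Outcomes; Data collection methods). No longer follow-up is given for the deferred arms. The figure and the supplementary schedule were not available to this review.

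The question posed in the Abstract is whether a booster before immunosuppression "provides greater anti-spike IgG-mediated immunity than a booster given 24 weeks after new or intensified immunosuppression".

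**The concern.** In Arms A and C the booster is given at week 0, so the two definitions coincide. In Arms B and D they are 24 weeks apart, and nothing in the article reconciles them.

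Each clock has its own difficulty. Twelve months from the booster runs past the end of follow-up in the deferred arms, so a booster-based average there covers only the early post-booster period, including the peak. Twelve months from week 0 gives the deferred arms about half a year without the booster, so the comparison mixes how well the booster worked with how long it had been on board.

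At stake is the headline conclusion on timing: the same data could favour either arm depending on which sentence the analyst follows. The trial is open-label, and the Interim analyses section plans an efficacy look at the primary endpoint when 160 participants have reached 12 months. The analysis plan need only be approved before data lock.

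**Working it through.** **The plan's own figure.** Inputs from Sample size: SD 0.12 log10, difference 0.13 log10, two-sided 5%, 40 per sub-stratum, hence 20 per arm at 1:1. Standard error = 0.12 × √(2/20) = 0.0379, and 0.13/0.0379 = 3.43. Power is Φ(3.43 − 1.96) = 92.9%, or 91.6% by the noncentral t with 38 df. Also 10^0.13 = 1.349, the stated 35%. The power statement reproduces; the fault lies in the endpoint definition.

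**Observable window in Arms B and D.** 48 − 24 = 24 weeks, or 52 − 24 = 28 if 12 months means 52 weeks. That is 50% to 54% of the stated 12 months. A full window would need follow-up to about week 72 to 76.

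**General result with identical boosters.** Let f(t) be the rise in log10 titre t weeks after a booster, the same in both arms, with the deferred arm flat until week 24. Let F(T) be the area under f from 0 to T.

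- Week 0-48 clock: immediate F(48)/48, deferred F(24)/48. The difference is [F(48) − F(24)]/48, which is half the mean residual rise in weeks 24-48 after a booster. A mean residual of 0.26 log10 therefore gives the whole 0.13 design difference.
- Booster clock on all available data: immediate F(48)/48, deferred F(24)/24.
- Booster clock cut to 24 weeks in every arm: the difference is 0.

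**One case in full (kinetics assumed, not in the documents).** Linear rise to 1.0 log10 over 4 weeks, then a 90-day half-life. Decay is 0.30103 × 7/90 = 0.02341 log10 per week, so the rise has gone at 4 + 1/0.02341 = 46.7 weeks.

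- F(48) = 2 + ½ × 42.71 × 1.0 = 23.36
- F(24) = 2 + 20 − 0.02341 × 20²/2 = 17.32
- Week 0-48 clock: 0.487 − 0.361 = **+0.126** (favours immediate)
- Booster clock, all data: 0.487 − 0.722 = **−0.235** (favours deferred)

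**Range, same formulas (immediate minus deferred, log10).**

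| Assumed rise and half-life | Week 0-48 clock | Booster clock, all data |
|---|---|---|
| 1.0, 90 days | +0.126 | −0.235 |
| 0.8, 150 days | +0.175 | −0.133 |
| 0.5, 90 days | 0.000 | −0.131 |
| 0.5, no waning | +0.250 | +0.021 |
| 1.0, no waning | +0.500 | +0.042 |

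With 20 per arm and SD 0.12, a difference of 0.126 is declared significant about 90% of the time and 0.175 about 99%. Shortening the rise to 2 weeks changes the first row of the week 0-48 column to 0.466 − 0.361 = 0.105, significant 77% of the time.

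**Reference titre for a matched window.** If deferred-arm titres fall by d log10 before week 24 and both boosters then add the same increment, a 24-week comparison adjusted only for the week-0 titre differs by d in favour of the immediate arm. Measured from each arm's own pre-booster sample, it differs by 0.

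**The case against.** **The statistics sections point one way.** Sample size and the analysis section both use change from baseline, so the booster wording may be loose summary. This is plausible, and it makes the repair easy. It does not remove a printed conflict in the primary outcome, which the Abstract and Outcomes share and the Objectives echo. A later analysis plan may choose between the definitions, but the choice has to precede any look at outcomes.

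**The booster-based AUC can still be calculated.** A reader might infer that it cannot be computed in the deferred arms. The documents do not support that: Sample size says that a time-weighted AUC accommodates varying follow-up, and the analysis applies the trapezoidal rule to whatever data exist. What is missing is the full 12-month window. The unequal windows then favour the deferred arm in every waning case shown.

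**Week 0-48 exposure is a fair comparison of strategies.** A reader might also infer that this AUC is biased towards early boosting. It is not a bias in itself. Timing is what is randomised, and time spent boosted is a real consequence of timing. The point stands only as a limit on interpretation: this AUC cannot by itself show which booster response is greater, which is how the Abstract and Objectives frame the question. The secondary outcomes on antibody kinetics and on modelling of boosting and decay cover that question only in part.

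**The size rests on assumed kinetics.** This is correct. The documents give no titre rise or half-life, and the week 0-48 difference runs from 0 to 0.50 log10 over the cases tried, the top of the range requiring no waning for 48 weeks.

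**Conclusion.** The point holds: the primary endpoint has two conflicting time origins, 24 weeks apart in Arms B and D, and must be reconciled. The full 12-month post-booster window is not available in those arms, where about 24 to 28 weeks can be seen. That limit is inferred from the 12-month visit span and the week-48 assessment, since the visit schedule itself was not available.

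The choice of clock can change the sign of the result with identical boosters: +0.126 against −0.235 log10 in the worked case, beside a design difference of 0.13. This assumes the stated kinetics, a deferred arm that stays flat before week 24, and the plan's SD. The week 0-48 advantage is zero if the boost has gone by about 24 weeks, and the booster-clock reversal disappears if there is no waning.

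**What to change.** Before outcome data are examined, and in any case before the interim efficacy analysis:

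1. Use one primary definition in the Abstract, Objectives, Outcomes, Sample size and statistical methods sections: time-weighted AUC change from baseline in log10 NAb over weeks 0-48 from randomisation. Label it as antibody exposure under each strategy.
2. Add a matched window as the first key secondary: time-weighted mean change in log10 NAb over the 24 weeks after the COVID-19 booster, relative to each arm's own pre-booster sample (week 0 in Arms A and C, week 24 in Arms B and D). Base any claim about which booster response is greater on this endpoint. Making it co-primary would raise a multiplicity question that the plan does not address.
3. Do the same for the anti-tetanus secondary in Group 1, which is also a change from baseline over 12 months and has the mirror-image problem, since Arm A receives the DT booster at week 24.

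The cost is wording, with no added participants; the visit schedule should be checked to confirm that samples cover both windows. The matched window has limits that should be stated. It depends on retention to week 24, its reference in the deferred arms is a post-randomisation measurement, and it compares different calendar periods, with possible intervening infections or different vaccine products.
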